## Abstract

**Background:**

Sleep disturbance is becoming increasingly recognised as a clinically important symptom in people with chronic low back pain (CLBP, low back pain >12 weeks), associated with physical inactivity and depression. Current research and international clinical guidelines recommend people with CLBP assume a physically active role in their recovery to prevent chronicity, but the high prevalence of sleep disturbance in this population may be unknowingly limiting their ability to participate in exercise-based rehabilitation programmes and contributing to poor outcomes. There is currently no knowledge concerning the effectiveness of physiotherapy on sleep disturbance in people with chronic low back pain and no evidence of the feasibility of conducting randomized controlled trials that comprehensively evaluate sleep as an outcome measure in this population.

**Methods/Design:**

This study will evaluate the feasibility of a randomised controlled trial (RCT), exploring the effects of three forms of physiotherapy (supervised general exercise programme, individualized walking programme and usual physiotherapy, which will serve as the control group) on sleep quality in people with chronic low back pain. A presenting sample of 60 consenting patients will be recruited in the physiotherapy department of Beaumont Hospital, Dublin, Ireland, and randomly allocated to one of the three groups in a concealed manner. The main outcomes will be sleep quality (self-report and objective measurement), and self-reported functional disability, pain, quality of life, fear avoidance, anxiety and depression, physical activity, and patient satisfaction. Outcome will be evaluated at baseline, 3 months and 6 months. Qualitative telephone interviews will be embedded in the research design to obtain feedback from a sample of participants' about their experiences of sleep monitoring, trial participation and interventions, and to inform the design of a fully powered future RCT. Planned analysis will explore trends in the data, effect sizes and clinically important effects (quantitative data), and thematic analysis (qualitative data).

**Discussion:**

This study will evaluate the feasibility of a randomised controlled trial exploring the effects of three forms of physiotherapy (supervised general exercise programme, individualized walking programme and usual physiotherapy, which will serve as the control group) on sleep quality in people with chronic low back pain.

**Trial Registration:**

Current controlled trial ISRCTN54009836

## Background

Sleep disturbance is becoming increasingly recognised in the literature as a clinically important symptom in people with chronic low back pain (CLBP, low back pain >12 weeks) [1-5]. A large prospective study found there was a highly significant relationship between pain and sleep (P < 0.0005), with a 55% increase in the proportion of participants reporting restless/light sleep after chronic low back pain onset [2]. Sleep disturbance has been found to have a negative effect on mood, pain severity experience and general quality of life [6,7]. Depression in particular is strongly associated with disturbed sleep patterns [8,9] and has been previously identified in sleep studies involving patients with chronic LBP [10-14]. The pain literature has shown that lack of sleep or poor quality sleep lowers the pain threshold and the mental capacity to manage pain [15,16], and it has been hypothesized that better daytime pain control may lead to improved sleep quality [17]. The current literature has identified that for certain patients' chronic pain, physical inactivity, sleep disorders and depression seem to be interdependent, and whether cause or consequence, LBP-related sleep problems should be addressed as an integral part of the management plan of each patient [4].

Current research and international clinical guidelines recommend people with CLBP to assume a physically active role in their recovery to prevent chronicity [18-23], but the high prevalence of sleep disturbance in this population may be unknowingly limiting their ability to participate in exercise-based rehabilitation programmes and contributing to poor outcomes. Internationally, physiotherapy services are frequently utilized by people with LBP, predominantly for the evidence-based approaches of advice, spinal manipulative therapy and exercise therapy [23-28]. However, there is currently no knowledge of the effectiveness of any physiotherapy approaches for sleep disturbance in people with chronic low back pain.

While both subjective and objective measures of sleep patterns have been widely used in sleep research in people with various sleep disorders (e.g. obstructive sleep apnoea and insomnia) for over two decades [29,30], they have not been previously utilized as outcome measures in LBP clinical trials. Several valid and reliable subjective sleep questionnaires are available (e.g. Pittsburgh Sleep Quality Index [31], Insomnia Severity Index [32]), and the most widely used objective sleep outcome measure for research in non-laboratory settings is actigraphy [30]. Recently, other novel non-contact measurement devices have been developed to measure sleep quality in the home environment [33,34].

This project will evaluate the feasibility of undertaking a randomised controlled trial (RCT) that will explore the effects on subjective and objective measures of sleep quality and low back pain outcomes, of three forms of physiotherapy management of low back pain, i.e. a supervised general exercise class, usual physiotherapy, and a novel walking programme. The supervised exercise programme is based on the "Back to Fitness" class, whose effectiveness has been supported in several RCTs, reporting significant improvements in pain and disability compared to 'routine' physiotherapy [35] and GP management [36], with comparable effects to spinal manipulative therapy [37]. The recent UK National Institute for Clinical Excellence guideline for persistent LBP advocates such a structured exercise programme as one of the cost effective management options for this condition [23]. Recent literature has identified the need for research of brief/minimal contact self-activation interventions, such as walking programmes that encourage participation in physical activity for CLBP [22,38]. Details of the walking programme utilized in this feasibility trial have been reported in detail elsewhere [39].

The objectives are

To determine the most efficient and effective design for a main RCT by:

• Piloting the methodological procedures

• Determining the recruitment rate and actual numbers recruited

• Determining attrition rates during the intervention and follow-up periods

• Completing a qualitative exploration of participants experience of the trial procedures, interventions, and outcomes

• Evaluating the feasibility of using equipment to measure sleep disturbance within a clinical trial setting

• Determining the prevalence of sleep disturbance in the sample

• Comparing changes in sleep quality, pain, function, quality of life, fear avoidance, physical activity and patient satisfaction between groups between baseline and follow-up

• Exploring the relationship between outcome changes and sleep quality

• Conducting a power calculation to determine the numbers needed for a future large-scale, multi-centre, randomised controlled trial

• Refining the protocol for a future large-scale, multi-centre, randomised controlled trial

## Methods/Design

The Research Ethics Committee of Beaumont Hospital has granted approval for this study: The trial will be reported according to the recommendations of the Consort statement [40] and the template for describing the flow of participants through the study is represented in Figure 1. The quantitative study will explore the effects of three forms of physiotherapy (i.e. a supervised general exercise programme, usual physiotherapy and a walking programme) on sleep for patients with chronic low back pain. The qualitative study will explore participants' experience of the study and the interventions.

**Figure 1 F1:**
[figure not shown]
**Participant flow through the RCT (based on CONSORT statement)**.

### Quantitative study

#### Design

The study will be a prospective feasibility randomized controlled trial (RCT) with three arms (i) a supervised exercise class of 8 weeks duration (ii) a walking programme of 8 weeks duration and (iii) usual physiotherapy. Outcomes will be assessed at baseline and 3 [face-to-face] and 6 month [pre-paid postage] follow-up.

#### Controlling bias

The RCT design includes key methodological features that have been recognized as important in minimizing bias in clinical trials: true randomization, concealed allocation, specification of eligibility criteria, and intention-to-treat analysis [41].

#### Setting

A sample of patients will be recruited in Beaumont Hospital physiotherapy department that provides physiotherapy treatment for people with CLBP in the Northside of Dublin City.

#### Protocol protection

The following mechanisms will be used to ensure the trial protocol is applied consistently: protocol manuals will be developed and all involved researchers and clinicians will be trained to ensure that participant screening, assessment, random allocation and treatment procedures are conducted according to the protocol; a random sample of 10% of treatment records in each group will be audited by a researcher not involved in the day to day running of the trial to check that treatment is administered as per the protocol; if any notable anomalies are found all treatment records will be checked. The treatment record forms will be completed by clinicians on every patient recruited to the study.

### Study population and recruitment

#### Clinics and clinicians

In preparation for the ethical approval and funding applications for the trial a meeting was held with the relevant physiotherapy department manager to outline the project and distribute the outline protocol. Information meetings were held with the manager and treating physiotherapists to discuss the study background, aims and methodologies and to address their queries. Reception staff were briefed on the study recruitment process, and patient appointment systems, paperwork and filing arrangements for the trial were explored.

Prior to commencement of the trial, all participating physiotherapists involved in the active interventions (i.e. supervised exercise class, walking programme) will attend training days in the School of Public Health, Physiotherapy and Population Science, University College Dublin to be delivered by various members of the research team. The main focus of the training days will be to ensure that the interventions are standardized and a cognitive behavioural therapy (CBT) approach will be emphasized. In advance of the training days, a detailed trial manual will be distributed to the therapists and their role in the study will be highlighted.

#### Patients

All eligible participants with chronic or recurrent LBP referred to the Beaumont Hospital physiotherapy department by general practitioners or hospital consultants will be invited to participate in the study by the Trial Co-ordinator in order of referral until the target sample (n = 60) is achieved (Table 1). They will receive the initial contact by letter containing the patient information leaflet outlining the trial procedures and an invitation to attend for baseline assessment. Suitable, interested participants, once screened by telephone, will attend the physiotherapy department, where detailed verbal explanations of the study protocol will be provided and, written informed consent will be sought by the Trial Co-ordinator. The Trial Co-ordinator will record the number of participants who were invited and declined, those considered ineligible and the reasons.

**Table 1 T1:** Eligibility Criteria

Inclusion criteria	Exclusion criteria
Patients with chronic (≥3 months) or recurrent (≥3 episodes in previous 12 months) LBP of mechanical origin with/without radiation to the lower limb	Clinically diagnosed primary sleep disorder e.g sleep apnoea, primary insomnia
Males/females between 18-70 years	Currently or having received treatment for CLBP within previous 3 months
No spinal surgery within the previous 12 months	Patients scoring <10 indicating minimum disability on the Oswestry Disability Index
Patients scoring ≥10 indicating moderate disability on the Oswestry Disability Index (ODI).	Red flags indicating serious spinal pathology, e.g. cancer, cauda equina lesion
Patients deemed suitable by their GP/hospital consultant to carry out an exercise programme	Radicular pain indicative of nerve root compression
Patients willing to attend for an 8-week treatment programme of exercise classes	Patients diagnosed with severe spinal stenosis, spondylolisthesis, fibromyalgia
Fluency in English (verbal and written)	History of systemic/inflammatory disease, e.g. rheumatoid arthritis
Access to a telephone (for follow-up support)	Patients with any confounding conditions such as a neurological disorder or currently receiving treatment for cancer
	Patients with acute (<6 weeks) or subacute LBP (6-12 weeks), provided that they have experienced <3 LBP episodes during previous 12 months
	Unstable angina/uncontrolled cardiac dysrhythmias/severe aortic stenosis/acute systemic infection accompanied by fever
	Medico-legal issues
	Pregnancy

### Eligibility assessment

#### Clinicians

Chartered Physiotherapists who are eligible for membership of the Irish Society of Chartered Physiotherapists and are employed in Beaumont Hospital are eligible to participate.

#### Patients

At the baseline interview the Trial Co-ordinator will use a screening checklist to verify eligibility (Table 1). Written signed consent will be obtained on all participants. The Physical Activity Readiness Questionnaire (PAR-Q)[42] will be completed to determine whether medical clearance is necessary before trial participation.

### Blinding

As this is a feasibility study blinding of the outcome assessor will not be possible but for a future main trial the outcome assessor and trial statistician would be blinded to group allocation until completion of data analysis. The Trial Co-ordinator will administer all outcome measures for face to face and postal follow-up. Due to the nature of the interventions under investigation it will not be possible to blind patients or clinicians to their group allocation in this feasibility study or a future main trial.

### Sample Size

No power-based sample size calculation has been carried out as this study aims to establish the feasibility of conducting a future multi-centre main trial of the same interventions. Recruitment will be on a consecutive basis, and will enable the researchers to estimate expected recruitment rates for the main RCT. Based on feasibility, the researchers aim to recruit 60 participants over a 6 month period at a rate of 10 per month. Based on the results of previous trials investigating physiotherapy for LBP [44], a 30% drop-out rate is anticipated between the beginning of treatment and the follow-up, so it is anticipated that n = 42 participants will complete the trial.

### Outcome measures

A combination of recommended self-report valid and reliable outcome questionnaires [45] that measure sleep quality, functional disability, pain, quality of life, physical activity, psychosocial and work loss variables, as well as objective measures of sleep quality will be completed at baseline, 3 month (face to face) and 6 month (postal) follow-up. An evaluation questionnaire regarding the utility of the objective sleep measures will be completed at baseline and the satisfaction questionnaire will only be completed at the 3 month follow-up point.

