#### Actiwatch (Model AW4, CamNTech, Cambridge, UK)

This is a small wrist-mounted device (37 × 29 × 10 mm; 16 grams), worn on the non-dominant wrist, which detects and logs movement intensity and duration by means of a small piezo-electric accelerometer. Using sleep analysis software it is capable of evaluating sleepwake patterns and common sleep quality variables: i.e. sleep onset latency, sleep efficiency and sleep fragmentation. It has been extensively validated against polysomnography, the 'gold standard' for sleep studies in healthy participants [59-62] and those with sleep disorders [63-65]. The Actiwatches will be set to average activity count data during recording at 10-sec epochs. Each participant will be requested to wear the Actiwatch on two separate occasions each lasting 7 nights as recommended by the American Academy of Sleep Medicine [66] at (i) baseline (starting the first night of recruitment), and (ii) 3 month follow-up either all day or from at least 30 min before they go to bed until at least 30 min after they wake up. After each 7-night period of sleep recording, participants will return the device to Beaumont Hospital in person or by courier, where data will be downloaded for analysis using the USB Actiwatch-reader and the Actiwatch Sleep v7.27 analysis software (CamNTech, Cambridge, UK). Before analysis, actigraphic data will be automatically converted to 30-sec epochs by the software and all sleep episodes will be visually inspected (scale: 1000) to screen for malfunctioning of the devices and non-wear time.

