#### Devices Utility Questionnaire

This is 7-item questionnaire designed to establish the utility (user-friendliness and its difficulties) of the objective sleep measures, adapted from a previously developed questionnaire [77]. Acceptability as a sleep measure, interference with sleep, wearing comfort, and awareness of wearing the device will be scored on 11-point numerical rating scales from 0 (not acceptable) to 10 (very acceptable). Participants will be requested to provide any free text comments on the use of the objective measures.

Participants will be phoned to request attendance at a face to face follow-up in the physiotherapy department at 3 months, and pre-paid postage envelopes will be sent at 6 months. Follow-up reminders will be given by phone and letter. Non-responders to the 3 month face to face follow-up will be requested to return completed questionnaires by pre-paid post or by telephone. A courier will be available to return the sleep monitoring devices unreturned by patients during the trial.

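### The device utility questionnaire is scheduled at baseline with no later administration, so the 3-month Actiwatch wear gets no structured rating

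*Protocol article*

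**What the plan says.** The objectives, listed at the end of the Background, include "Evaluating the feasibility of using equipment to measure sleep disturbance within a clinical trial setting".

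The Outcome measures section first gives the general schedule of baseline, 3 months and 6 months. It then names two instruments that depart from it. For the device form it says: "An evaluation questionnaire regarding the utility of the objective sleep measures will be completed at baseline". For the other it says that "the satisfaction questionnaire will only be completed at the 3 month follow-up point".

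The Actiwatch section says: "Each participant will be requested to wear the Actiwatch on two separate occasions each lasting 7 nights". The two occasions are "baseline (starting the first night of recruitment), and (ii) 3 month follow-up". It adds: "After each 7-night period of sleep recording, participants will return the device to Beaumont Hospital in person or by courier".

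The Devices Utility Questionnaire section describes a 7-item form adapted from an existing one. "Acceptability as a sleep measure, interference with sleep, wearing comfort, and awareness of wearing the device will be scored", it says, on a 0 to 10 scale with a single anchor pair running from not acceptable to very acceptable. The section also asks for free-text comments. It gives no time of administration.

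**The concern.** A feasibility trial should show whether a measurement can be used as an outcome in the main trial. For actigraphy, that means whether participants tolerate wearing the device at follow-up as well as at enrolment. Tolerance may differ on a second request, when novelty has gone and treatment has ended. The plan sets no occasion on which a participant rates the second wear, so a change in comfort, interference or acceptability between wears cannot be estimated. These ratings cannot be recovered once the trial is over.

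The anchors raise a smaller matter. Acceptability and comfort sit naturally on a scale from not acceptable to very acceptable. Interference with sleep and awareness of the device are matters of degree, and respondents may not all use an acceptability scale for them in the same way.

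**Working it through.** **Inputs**
- Scheduled times for the utility questionnaire: baseline (Outcome measures).
- Actiwatch wears: 2, each of 7 nights, at baseline and 3 months (Actiwatch section).
- Target sample 60, recruited at 10 per month over 6 months; anticipated drop-out 30%; 42 expected to complete (Sample Size).

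**The plan's own figures**
- 10 × 6 = 60.
- 60 × (1 − 0.30) = 42. Both reproduce.

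**Nights covered by a rating, per participant**
- Planned nights: 2 × 7 = 14.
- Form completed at device return after the first recording: 7 of 14 nights rated.
- Form completed at the baseline visit itself: 0 of 14 nights rated.
- On either reading, 0 of the 7 nights at 3 months are rated.

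**Second wears left unrated**
- If the whole 30% loss has occurred by 3 months (assumption): 60 × 0.70 = 42.
- If no loss has occurred by 3 months (assumption): 60.
- As a share of all wear periods: 42 / (60 + 42) = 41% in the first case and 60 / (60 + 60) = 50% in the second.

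Both cases assume that everyone still in the trial wears the device. The number could be below 42, because those who do not attend at 3 months are asked only to return questionnaires by post or telephone.

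**What else reaches the 3-month wear**
- Free-text comments: part of the utility questionnaire, so they follow its schedule and do not reach it.
- Recorded difficulties with the monitoring equipment: tabulated with no restriction to baseline (Data Analysis), so they can cover it. They capture problems that someone reports and records, not a rating from every wearer.
- Visual inspection of recordings for malfunction and non-wear: applies to all recordings (Actiwatch section), so it covers it. It shows whether the device was worn, not how it was experienced.
- Telephone interviews: all participants are invited, and views on sleep monitoring are a main topic (Qualitative study). They follow the 6-month follow-up, so about three months after the second wear (6 − 3 = 3), and are qualitative.

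None of these yields a number that can be set beside the baseline ratings.

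**Anchors**
Taken literally, 10 means very acceptable for every item, so all four stated constructs run in one direction. The difficulty is one of fit: a participant who had no interference is asked how acceptable it was, not how much there was.

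**The case against.** Three stronger readings are tempting, and the protocol supports none of them.

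First, a reader might infer that the form is completed before anyone has worn the device, since the first wear starts on the night of recruitment. The protocol says baseline, not the baseline visit, and it labels the whole first 7-night recording as baseline. Device return after that week is an obvious moment for a form about wearing comfort. The timing relative to the first wear is unstated; it is not stated to precede it.

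Second, a reader might infer that the equipment objective is left without usable evidence. It is not. Recorded difficulties, non-wear screening and interviews all bear on the second wear. Whether participants will wear the device again is answered directly by the 3-month recordings. The criterion against a main trial refers to participant feedback in general and is not tied to this questionnaire.

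Third, a reader might infer that the interference and awareness ratings cannot be interpreted. Read literally, the scale has one direction, and the article summarises an adapted form whose item wording is not shown. How many respondents would reverse the scale is unknown, so no size can be put on any distortion.

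It is also fair to say that the word 'only' qualifies the satisfaction questionnaire and not the utility form. Even so, the sentence lists exceptions to the general schedule, and no section gives the utility form a second time point. Baseline alone is the natural reading.

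What survives is that the follow-up wear has no scheduled structured rating, and that the anchor wording is loose for two constructs.

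**Conclusion.** The point holds in limited form. One of the two planned wear periods, the one that provides the objective follow-up measurement, has no structured participant rating. That is half of the 14 planned nights per participant, and about 42 second wears if the full 30% loss has occurred by 3 months and all who remain wear the device.

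This rests on reading baseline as the form's sole time point and on the Actiwatch section's count of two wears. The general sentence in Outcome measures could be read as placing objective sleep measures at 6 months too; a wear then would also be unrated.

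The anchor issue is a secondary wording point. Overall this is minor to moderate: it limits what the trial can say about tolerance of actigraphy at follow-up, and it leaves the PSQI, the ODI, the effect sizes and the main-trial power calculation untouched.

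**What to change.** In Outcome measures, state that the utility questionnaire is completed when the Actiwatch is returned after each 7-night recording, at baseline and at 3 months, and that both sets of ratings will be reported. This also settles whether the form precedes or follows the first wear. Report the 3-month ratings with the number who did the second wear, because they come only from those participants.

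In the Devices Utility Questionnaire section, give interference and awareness their own anchors, for example 0 for none to 10 for extreme, and state which direction is favourable. If the form itself already has item-specific anchors, the article's description should say so.

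The cost is one extra 7-item form per participant at a contact that already exists. The main limitation is that the second rating will be selective, since those who drop out or decline the second wear will not supply it. The existing record of difficulties and the interviews should therefore be kept alongside it.
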